### Criteria for discontinuing or modifying allocated interventions {11b}

This is not applicable as the intervention is to improve medication adherence, so there will be no special criteria for discontinuing or modifying allocated intervention.

### Strategies to improve adherence to interventions {11c}

The various interventions are for the improvement of adherence as measured by the Morisky Medication Adherence scale [21].

### Relevant concomitant care permitted or prohibited during the trial {11d}

Relevant concomitant care is permitted.

### Provisions for post-trial care {30}

This is a non-pharmacological intervention; therefore, there are no specific post trial care provisions. 

### Outcomes {12}

#### Primary, secondary, and other outcomes

The primary outcome is the adherence of patients as measured by Morisky adherence scale [21] at the beginning of the study, midterm, and at the end. The secondary outcomes include Quality of Life (EuroQOL) [22], blood pressure, random blood sugar, HbA1c among the cardiac patients with type 2 diabetes, mortality events, and other unintended outcomes will also be recorded. The analysis will include change from baseline. Adherence is chosen as the main outcome as the objective is to study the impact of the various interventions singly and in combination on adherence in comparison to standard of care. Various symptoms, such as dyspnea, fatigue, edema, difficulty sleeping, depression, and chest pain associated with CVD limits activities of daily life [23]. Therefore, it is important to measure the quality of life before and after the intervention. Metabolic control can result from better adherence to medication and a better awareness of the importance to adhering to medication. Therefore, meeting targets of blood pressure, blood sugar levels, and HbA1c will be considered as secondary outcomes.

### Participant timeline {13}

**Table 1 Tab1:** Timeline of activities

**Study period**	**Enrollment**	**Allocation**	**Post allocation**						Close-out
			**Month 1**	**Month 2**	**Month 3**	**Month 4**	**Month 5**	**Month 6**	
**Enrollment**									
Eligibility screen	♦								
Informed consent	♦								
Allocation		♦							
**Interventions**									
Intervention A			♦	♦	♦	♦	♦	♦	
Intervention B			♦	♦	♦	♦	♦	♦	
Intervention C			♦	♦	♦	♦	♦	♦	
Intervention D			x	x	x	x	x	x	
**Assessments**									
Baseline assessment	♦	♦							
Primary outcome									♦
Secondary outcome									♦

### Sample size {14}

Based on the learnings from the previous study, the rate of missing data due to electronic data collection will be low.

#### Phases 1 and 2: planning and baseline evaluation

The process of developing the intervention will start with the development of the initial concepts based on the available literature and interaction with healthcare professionals working in the rural areas.

## Baseline study

*Selection and training of team*: The team will deliver the training to the selected project coordinator and the field staff. Field staff (part-time) will be recruited by the investigators on the advice of village head and/or NCD clinic in-charge. He/she should be a member of community preferably the accredited social health activist with an interest in health care and community, willingness to learn, and leadership qualities. A strong commitment to work in the community will be identified as an important criteria for the selection of all the team members. After a sensitization session of the data collectors/field staff, they will be asked to prepare a list of persons with cardiovascular disease including coronary artery disease, valvular disease, arrhythmias, and heart failure. Hands on sessions to download the App and collect data will be provided.

In Phase 2, baseline evaluation will be initiated in the study areas after obtaining the ethics committee approval. Written informed consent will be obtained from the study participants. Participants will receive a participant information sheet (PIS) outlining the rationale for the study, details on interventions, the steps, and protocols to be followed throughout the study, potential side effects and risks, benefits, a confidentiality statement, the option to withdraw from the study at any time, and the investigators’ contact information. The baseline survey performed by ASHAs will be done through a survey app called SHRADDHA. The variables collected would include (1) basic demographic information, including age, income, gender, marital status, religion, and occupation; (2) lifestyle-related factors such as physical activity, tobacco use, and alcohol consumption, dietary factors intake of fruits and vegetables, cooking oil and red meats; (3) disease details including for diabetes, hypertension, dyslipidemia, stroke and CAD, COPD, and surgeries; and (4) current medications. Questions will be explained to each participant to help them get familiar with the contents, instructions for filling them out will be given, and the responses will be recorded. On the home visit, the Field staff/ASHA will also record height and weight, measure sugars with a glucometer, and take a photo of the most recent prescription. All of this will be recorded in the app. Glycosylated hemoglobin will also be measured among the cardiac patients with diabetes using the point of care device called Lumira Dx.

*Sample size*: Sample size was estimated assuming an improvement of 10% in medication adherence at the end of a 6-month period in either m-health or community health worker-led intervention compared to control group. This 10% improvement will lead to an effect size of 0.4 units in medication adherence through m-health or community health worker-led intervention and an effect size of 0.8 units in combined intervention (m-health and community health worker-led intervention) compared to the control group. The 10% was an assumption considering that large differences are not possible in a community setting and was based on another community-based study which has also used 10% improvement of adherence score [24].

To observe a difference of 0.4 units in the medication adherence between study groups, with a standard deviation of 1.8, 5% level of significance (adjusted for multiple comparison) and 80% power, the sample size needed will be 238 participants in each of the study groups. After accounting for a design effect (cluster effect) and 10% attrition, the number of participants required per group will be 393, a total of 1572 participants.

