**Methods:**

The intervention is a 2 × 2 factorial design trial applying two interventions individually and in combination with 1:1 allocation ratio: (i) ASHA-led medication adherence initiative comprising of home visits and (ii) m-health intervention using reminders and self-reporting of medication use. This design will lead to four potential experimental conditions: (i) ASHA-led intervention, (ii) m-health intervention, (iii) ASHA and m-health intervention combination, (iv) standard of care. The cluster randomized trial has been chosen as it randomizes communities instead of individuals, avoiding contamination between participants. Subcenters are a natural subset of the health system, and they will be considered as the cluster/unit. The factorial cluster randomized controlled trial (cRCT) will also incorporate a nested health economic evaluation to assess the cost-effectiveness and return on investment (ROI) of the interventions on medication adherence among patients with CVDs. The sample size has been calculated to be 393 individuals per arm with 4–5 subcenters in each arm. A process evaluation to understand the effect of the intervention in terms of acceptability, adoption (uptake), appropriateness, costs, feasibility, fidelity, penetration (integration of a practice within a specific setting), and sustainability will be done.

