### Trial design {8}

It is a 2 × 2 factorial design trial applying two interventions individually and in combination with a 1:1 allocation ratio. Two interventions are applied individually and in combination: (i) ASHA-led medication adherence initiative comprising of home visits, and (ii) m-health intervention using reminders and self-reporting of medication use. This design will lead to four potential experimental conditions: (i) ASHA-led intervention, (ii) m-health intervention, (iii) ASHA and m-health intervention combination, (iv) standard of care.

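### The 238 per group does not follow from the inputs printed with it; for either single intervention against control those inputs need 318 unadjusted and about 424 after adjustment for three comparisons

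*Protocol article*

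**What the plan says.** The sample size paragraph of the protocol article (under Baseline study) assumes an improvement "in either m-health or community health worker-led intervention compared to control group", worth 0.4 units for each single intervention and 0.8 units for the combination. The aim of the calculation is put as "To observe a difference of 0.4 units in the medication adherence between study groups". The SD is taken as 1.8 units. The error rates are given as "5% level of significance (adjusted for multiple comparison) and 80% power". From these the paragraph concludes that "the sample size needed will be 238 participants in each of the study groups". It then allows for clustering, through a design effect whose value is not given, and for attrition of 10%. The result of that step reads "the number of participants required per group will be 393, a total of 1572 participants". The abstract repeats it: "The sample size has been calculated to be 393 individuals per arm".

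Three other sections bear on which comparison is meant:

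- Objectives {7} sets each intervention, and the combination, against control.
- Trial design {8} says "It is a 2 × 2 factorial design trial applying two interventions individually and in combination with a 1:1 allocation ratio".
- Statistical methods {20a} models change in the Morisky score, with random cluster effects and fixed effects for ASHA and for m-health.

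**The concern.** The paragraph prints every main input of a two-group comparison of means, so its result can be checked, and it is too small. An adjustment for multiple comparisons can only raise the required number, yet 238 lies below the figure for a single unadjusted test.

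The power claim for the primary outcome rests on this number, and so do 393 per arm and the total of 1572. If the stated 80% is taken at face value, a null result for ASHA alone or m-health alone against control would be read as better evidence of no effect than the design can supply.

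**Working it through.** **Inputs from the sample size paragraph.** Difference d = 0.4; SD = 1.8; power 80% (z = 0.842); 5% level, described as adjusted. Sidedness, adjustment method and number of comparisons are not stated. I take two-sided as the main case. I take three comparisons with control from Objectives {7}, and show the range.

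**Step 1: try to reproduce 238.** n per group = 2(z_a + z_b)² SD²/d², where 2 × 3.24/0.16 = 40.5.

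| Level | z_a | n per group |
|---|---|---|
| two-sided 0.05 | 1.960 | 40.5 × 2.802² = 317.9, so 318 |
| two-sided 0.05/2 | 2.241 | 385 |
| two-sided 0.05/3 | 2.394 | 40.5 × 3.236² = 424 |
| two-sided 0.05/6 | 2.638 | 491 |
| one-sided 0.05, unadjusted | 1.645 | 250.4, so 251 |

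Dunnett's method for three comparisons with control gives about 412. No row gives 238, which is 25% below 318 and 44% below 424.

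**Step 2: the inflation.** 393 × 0.9/238 = 1.49 and 393/(1.1 × 238) = 1.50. The implied design effect is therefore about 1.5, and 393 per arm corresponds to about 238 effective participants. The total is right: 4 × 393 = 1572.

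**Step 3: power for one intervention against control at 238 effective per group.** The standard error is 1.8 × √(2/238) = 0.165, and 0.4/0.165 = 2.424.

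- Unadjusted: Φ(2.424 − 1.960) = 0.68.
- At 0.05/3: Φ(2.424 − 2.394) = 0.51.
- With t on 14 df (18 subcenters less 4 arms): about 61% and 39 to 41%. The range reflects the approximation used.
- Difference detectable with 80% power (normal approximation): 2.802 × 0.165 = 0.46 unadjusted; 3.236 × 0.165 = 0.53 at 0.05/3.

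**Step 4: does the inflation absorb the gap?** After 10% attrition, 393 leaves 393 × 0.9, about 354. That covers 318 only if the design effect is at most 354/318 = 1.11. It does not cover 424 even with no clustering (power about 71% at 0.05/3).

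**Step 5: the factorial main effect.** Two cells are compared with two cells, so the n per cell is half that in step 1: 159 unadjusted, 193 at 0.05/2, 212 at 0.05/3, 226 at 0.05/4, 237 at 0.05/5, 246 at 0.05/6. Only a five-fold adjustment comes near 238. Power with 2 × 238 = 476 effective per margin: 0.4/(1.8 × √(2/476)) = 3.428, so Φ(3.428 − 1.960) = 0.93 unadjusted and Φ(3.428 − 2.394) = 0.85 at 0.05/3. With 14 df these become about 89% and 76%.

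**Step 6: baseline adjustment.** With baseline–endline correlation 0.5, adjustment multiplies n by 1 − 0.5² = 0.75, and 317.9 × 0.75 = 238.4. This matches 238, but only with no multiplicity adjustment.

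**The case against.** The strongest reply is that this is a factorial trial. The assumed effects are additive (0.4, 0.4, 0.8), and Statistical methods {20a} fits factor effects. A margin test at alpha 0.01, computed with the t distribution, even rounds up to 238 per cell. What stands is that the power shortfall cannot be asserted for every comparison: the main effects are adequately powered by normal approximation. What does not stand is that this explains 238. No five-fold adjustment is described, and both the objectives and the sample size paragraph define the effects against the control group.

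A second reply is that a baseline correlation was assumed. Correlation 0.5 with baseline adjustment gives 238, and so does an analysis of raw change with correlation 0.625 if 1.8 is the SD at a single time point, since 2(1 − 0.625) = 0.75. The protocol does not say which SD 1.8 is. Neither correlation is stated, and both routes need an unadjusted test, contrary to the paragraph.

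A third reply is that an article may leave the design effect and intracluster correlation to the full protocol. That is fair, and their absence alone is no finding. The point here is that printed inputs and printed output disagree.

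A reader might infer from 238 × 1.5 × 1.1 = 392.7 that attrition was applied wrongly. The document does not support this: a design effect of 1.49 with division by 0.9 gives 393 equally well.

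**Conclusion.** The figure 238 is wrong for the comparison that the paragraph describes. For either single intervention against control, the stated inputs need 318 per group unadjusted and about 424 at 0.05/3 (385 to 491 for two to six comparisons). The gap exists whatever the number of comparisons, because one unadjusted test already needs 318, or 251 one-sided.

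At 393 per arm, power for 0.4 units in that comparison is about 68% unadjusted or 51% at 0.05/3, and lower with 14 df, instead of 80%. These power figures rest on an inferred design effect of about 1.5, two-sided testing and no gain from baseline adjustment.

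A reader might infer that the whole trial is underpowered or that enrolment must rise. The document does not support that. The combination against control (0.8 units) needs only 80 per group unadjusted or 106 at 0.05/3, and the factorial main effects have about 93% or 85% power by normal approximation. The established fault is a sample size that its own inputs contradict, in a paragraph whose comparison differs from the factor effects listed in the analysis section.

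**What to change.** Keep enrolment at 393 per arm. In the sample size paragraph, name the comparison that is powered, and give its power and detectable difference together with the sidedness, number of comparisons and adjustment method, design effect, and any baseline correlation used.

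- **If each single intervention against control is powered:** about 68% power for 0.4 units unadjusted, or about 51% at 0.05/3; detectable difference 0.46 or 0.53 units. Add the lower figures for 18 clusters (about 61%, and 39 to 41%).
- **If the factorial main effects are powered:** about 93% unadjusted or 85% at 0.05/3 (about 89% and 76% with 14 df). Align the objectives and the effect-size sentence with that choice.
- **If 238 came from baseline adjustment with correlation about 0.5:** say so, make the primary analysis baseline-adjusted, and reconcile this with the statement that the level was adjusted.

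In the abstract, 393 can stand as the enrolment but should not be described as the result of this calculation. The cost is rewording and, on the pairwise reading, a less favourable stated power. No extra participants are needed.

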## Methods: participants, interventions, and outcomes

### Study setting {9}

The study will be implemented in the ENDIRA (Epidemiology of Non-communicable Diseases in Rural Areas) cohort (n-114,064 individuals) which includes 2064 patients with heart disease in whom adherence to drugs for heart disease has already been assessed. The ENDIRA cohort is spread over 5 primary health centers consisting of 18 subcenters where the health details of all individuals have been recorded. In order to avoid contamination in the treatment allocation and its response, at least 10 km of distance among villages will be maintained and they will be clubbed into 4 groups.

The intervention will be implemented in Angamaly block consisting of five local self-government areas namely Mookkannoor, Kalady, Thuravoor, Karukutty, and Manjapra with a population of 18,638, 20,407, 20,475, 26,811, and 14,668 in Ernakulam district [20] in Kerala state, India, respectively.

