## Assignment of interventions: allocation

### Sequence generation {16a}

Allocation of intervention and sequence generation will be as follows. Codes will be randomly assigned to the four interventions (ASHA, m-health, ASHA + m-health, and control groups) namely A, B, C, and D. In the next step, randomization list will be generated using RANDOM ALLOC software. Eighteen subcenters will be randomized into 4 study groups (A, B, C, and D) using different permutations of ABCD. Each subcenter will be allocated random numbers ranging from 1 to 18 using random number generators and random shuffling of this number. Interventions will be allocation to the subcenters in the sequence of random shuffled numbers as per the randomization list.

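### With 18 subcenters, the stated 80% power for a single-intervention-versus-control comparison is about 74%, even if 238 per group and the implied design effect are accepted

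*Protocol article*

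**What the plan says.** The sample-size paragraph (under Baseline study) sets its target as follows: "To observe a difference of 0.4 units in the medication adherence between study groups". The SD is given as 1.8, and the error rates are stated as "5% level of significance (adjusted for multiple comparison) and 80% power". From these it obtains 238 per group. The next sentence reads "After accounting for a design effect (cluster effect) and 10% attrition, the number of participants required per group will be 393, a total of 1572". The same paragraph assumes 0.4 units for either intervention alone and "an effect size of 0.8 units in combined intervention", each against control.

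The number of randomized units is fixed elsewhere. The Abstract says "The sample size has been calculated to be 393 individuals per arm with 4–5 subcenters in each arm", and Sequence generation {16a} says "Eighteen subcenters will be randomized into 4 study groups (A, B, C, and D) using different permutations of ABCD". Statistical methods {20a} plans mixed models for differences between the four groups, with random effects for clusters and fixed effects for ASHA and for m-health. The primary objective compares each intervention, and the combination, with control.

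**The concern.** Multiplying an individually randomized sample size by a design effect corrects the variance for clustering. It does not correct the reference distribution. When few clusters are randomized, the between-cluster variance is estimated on few degrees of freedom, so the test uses a t quantile and power falls below what the normal approximation gives. With 4 to 5 subcenters per arm this loss is not negligible.

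At stake is how a null result is read. If ASHA alone or m-health alone shows no significant difference from control, readers will judge it against a claimed 80% power that the pairwise comparison does not have. Because the number of subcenters is fixed at 18, the claim also depends heavily on the ICC staying very small.

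**Working it through.** **Inputs from the protocol.** 238 per group before inflation; 393 per group and 1572 in total after it; 10% attrition; 80% power; 5% significance; difference 0.4; SD 1.8 (all from the sample-size paragraph). 18 subcenters in four arms (Sequence generation; Abstract). Two-sided testing is assumed, as the protocol does not state it.

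**1. Reproduce the inflation step.**
- Attrition as a multiplier: 238 × 1.5 × 1.10 = 392.7, which rounds to 393. Design effect = 393 / 1.10 / 238 = 1.50.
- Attrition as a divisor: design effect = 393 × 0.9 / 238 = 1.49.
- 393 × 4 = 1572.

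The step reproduces under a design effect of about 1.5.

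**2. Implied ICC.** Cluster size is 1572 / 18 = 87.3 enrolled, or 87.3 × 0.9 = 78.6 completers. From ICC = (design effect − 1) / (m − 1):
- completers: 0.50 / 77.6 = 0.0064
- enrolled: 0.486 / 86.3 = 0.0056

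**3. Power on the plan's own terms.** Accepting that 238 effective participants per group give 80% with normal quantiles, the noncentrality is 1.960 + 0.842 = 2.802. Between-cluster degrees of freedom with all four arms in the model are 18 − 4 = 14, so the critical value rises from 1.960 to 2.145. Noncentral t power is then 0.741, about 74%.

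If the adjustment for multiple comparisons means 0.05/3, and 238 is taken to give 80% at that level, the noncentrality is 3.236 and the critical value with 14 df is 2.718. Power is 0.694, about 69%.

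**4. Sensitivity to the ICC (values above 0.0064 are assumptions).** Completers per arm are 393 × 0.9 = 353.7. Design effect = 1 + 77.6 × ICC. Noncentrality = 2.802 × √(353.7 / design effect / 238).

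| ICC | Design effect | Effective n per arm | Noncentrality | Pairwise power, 14 df |
|---|---|---|---|---|
| 0.0064 | 1.50 | 236 | 2.792 | 74% |
| 0.01 | 1.78 | 199 | 2.563 | 66% |

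**5. Pooled factorial contrasts.** Comparing 9 with 9 subcenters, without an interaction term, leaves 18 − 3 = 15 df (critical value 2.131) and multiplies the noncentrality by √2. The SD basis must be kept consistent. Accepting 238 at two-sided 5% implies an SD of 0.4 × √(238/2) / 2.802 = 1.56, not 1.8, so both bases are shown for ICC 0.0064.

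| Basis | Noncentrality | Pooled power, 15 df |
|---|---|---|
| 238 accepted (SD 1.56) | 2.792 × √2 = 3.948 | 96% |
| Stated SD 1.8 | 0.4 / (1.8 × √(2 × 1.497 / 353.7)) × √2 = 3.416 | 89% |

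**The case against.** The strongest reply is that this is a factorial trial. The statistical methods section fits fixed effects for ASHA and for m-health, and the assumed effects (0.4, 0.4 and 0.8) are additive. On that reading each effect draws on all 18 subcenters, and power exceeds 80% at the implied ICC. This stands, and it limits the point to pairwise contrasts. A reader might infer that 18 subcenters cannot deliver 80% power for the trial at all; the documents do not support that. It does not remove the point, because the sample-size paragraph sizes a 0.4-unit difference between study groups, and the primary objective compares each intervention with control.

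A second reply is that a journal article need not print the ICC or the degrees-of-freedom method. That is right, and their absence is not the complaint. The printed 238, 393, 10% and 18 subcenters are enough to test the stated 80%.

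Two stronger readings should also be set aside. Using only the two compared arms (4 versus 5 subcenters, 7 df) would give 67%, but the planned model includes all four groups, so 14 df is the appropriate figure. Much larger losses follow from ICCs of 0.02 or 0.05 (51% and 30% pairwise, 14 df, 238 accepted). No ICC appears in the protocol, and nothing in it shows that 0.006 is too low.

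**Conclusion.** The point holds for the pairwise comparisons. On the plan's own 238, design effect and attrition, the power for a 0.4-unit single-intervention-versus-control difference is about 74% instead of 80%, a loss of about 6 percentage points that needs no outside figure. At 0.05/3 it is about 69%, a loss of about 11 points. Any ICC above 0.006 adds to the loss, but how much rests on an assumed value.

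The result assumes two-sided testing, roughly equal cluster sizes, all four arms in one model, and no gain from baseline adjustment beyond what the plan's SD already includes. The 393 is not an arithmetic slip: the step reproduces. What is wrong is the power attached to it for this contrast. Whether 238 follows from a difference of 0.4 and an SD of 1.8 is a separate question, and the 74% does not depend on it.

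**What to change.** In the sample-size section:

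- Name the contrast to which the 80% applies.
- Restate power for each single-intervention-versus-control comparison using t quantiles with the between-cluster degrees of freedom.
- Give the power of the pooled ASHA versus no-ASHA and m-health versus no-m-health contrasts beside it.
- Use one SD throughout and show results over a stated ICC range.
- Do not claim 80% for the pairwise contrasts unless that calculation supports it.

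The cohort data can inform the ICC range, since Study setting {9} describes "2064 patients with heart disease in whom adherence to drugs for heart disease has already been assessed". The limits of that source should be stated. A single 2019 survey gives the ICC of adherence level, whereas the primary dependent variable is change. The Background describes those surveyed as coronary artery disease patients, whereas the trial also enrols patients with valve disease, rhythm disorders and heart failure.

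The cost is one variance-component estimate on existing data and a revised paragraph. No extra enrolment is needed. The downside is a less favourable stated power for the pairwise comparisons.
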